## Abstract

**Background:**

The economic burden of physical inactivity in Canada is estimated at Can $6.8 billion (US $5 billion) per year. Employers bear a substantial proportion of the economic costs, as they pay more for inactive workers in health care and other organizational costs. In response, many Canadian employers offer wellness programs, though these are often underutilized. While financial health incentives have been proposed as one way of increasing participation, their longer term effects (ie postintervention effects) are not clear.

**Objective:**

The objective of this paper is to outline the methodology for a randomized control trial (RCT) examining the longer term impact of an existing physical activity promotion program that is enhanced by adding guaranteed rewards (Can $1 [US $0.74] per day step goal met) in a lower active hospital employee population (less than 10,000 steps per day).

**Methods:**

A 12-week, parallel-arm RCT (with a 12-week postintervention follow-up) will be employed. Employees using Change4Life (a fully automated, incentive-based wellness program) and accumulating fewer than 10,000 steps per day at baseline (weeks 1 to 2) will be randomly allocated (1:1) to standard care (wellness program, accelerometer) or an intervention group (standard care plus guaranteed incentives). All study participants will be asked to wear the accelerometer and synchronize it to Change4Life daily, although only intervention group participants will receive guaranteed incentives for reaching tailored daily step count goals (Can $1 [US $0.74] per day; weeks 3 to 12). The primary study outcome will be mean proportion of participant-days step goal reached during the postintervention follow-up period (week 24). Mean proportion of participant-days step goal reached during the intervention period (week 12) will be a secondary outcome.

**Results:**

Enrollment for the study will be completed in February 2017. Data analysis will commence in September 2017. Study results are to be published in the winter of 2018.

**Conclusions:**

This protocol was designed to examine the impact of guaranteed rewards on physical activity maintenance in lower active hospital employees.

**ClinicalTrial:**

ClinicalTrials.gov NCT02638675; https://clinicaltrials.gov/ct2/show/NCT0 2638675 (Archived by WebCite at http://www.webcitation.org/6g4pvZvhW)

## Introduction

There is a substantial economic burden associated with physical inactivity in Canada [1,2]. According to Janssen [1], the cost of inactivity is Can $6.8 billion (US $5.0 billion) per year, posing a significant threat to the sustainability of the Canadian health care system. On the other hand, the projected cost savings of increasing the proportion of Canadians who meet physical activity guidelines (ie, 150 minutes of moderate-vigorous physical activity [MVPA] per week, or roughly 10,000 steps per day) by just 1% is Can $2.1 billion (US $1.6 billion) per year [3]. Notably, significant reductions in health risk and associated costs and improvements in quality of life are seen when inactive (<5000 steps per day) and low active (5000 to 7499 steps per day) adults become a little more active (eg, 1000 more steps per day) [3,4]. The workplace is an ideal setting for physical activity promotion since Canadian jobs are increasingly desk-based and sedentary [5].

Not surprisingly, Canadian employers bear a significant proportion of the inactivity burden because they pay more for lower active (<10,000 steps per day) workers in health care expenses [6]. For instance, while Canadian provincial and territorial governments cover hospital- and physician-related medical costs, employers in Canada often subsidize other medical expenses, one of the costliest being chronic disease–related medications [6]. A study by Wang and colleagues [7] helps to illustrate the economic benefit of a more physically active employee population. This study found that moderately active (1 to 2 times per week) and very active (3 or more times per week) employees had Can $250 (US $185) less paid health care costs annually when compared to their sedentary counterparts (0 times per week). In addition, wellness initiatives that increase employees’ physical activity have been shown to reduce absenteeism, presenteeism, and turnover [8-11]. Finally, according to health care surveys by Towers Watson [12] and Sanofi [6], Canadian employers have a vested interest in employees’ physical activity levels given the positive effects on organizational costs (eg, health care expenses) and performance (eg, presenteeism).

As a result, the majority (72%) of large Canadian companies now offer wellness programs to help reduce overall health care spending and increase productivity [6]. For participating employees, such programs have been associated with a reduced risk of chronic illness and lower medical claim costs [13,14]. However, these programs are chronically underutilized. In Canada, wellness program participation rates are extremely low, less than 10% [6]. This means that more than 90% of eligible Canadian workers are not reaping the benefits of company-sponsored wellness programming. Behavioral economics, a new branch of economics that is complemented by insights from psychology, has stimulated renewed interest in financial health incentives as a means to increase wellness program participation [5,15-17].

Behavioral economics recognizes that human decisions are biased in systematic ways and that that these “decision biases” can be leveraged to facilitate healthy decision making [18]. For example, according to behavioral economics, increasing the immediately rewarding aspects of a healthy behavior (eg, with a financial incentive) may offset the so-called “present bias” where people tend to overweigh the immediate costs (and discount the future benefits) of those behaviors (eg, time out of a busy schedule to exercise) [19]. Systematic reviews by Mitchell et al [20] and Strohacker et al [21] support the theory suggesting that incentives generally stimulate physical activity in the short-term (less than 3 months) and while incentives are in place. These reviews also suggest that not enough studies have examined the longer term (ie, postintervention) impact of incentives on physical activity to draw conclusions about sustained effects [20,21]—an issue of particular interest to Canadian employers looking to deliver cost-effective incentive-based wellness programs [5,6].

Of the randomized controlled trials (RCTs) that have recently examined this issue [22-26], 4 have observed a regression to baseline behaviors after incentive removal [22-24,26] and only 1 has demonstrated persisting physical activity [25]. One reason for this may have to do with the limited application of health behavior change theories in the design of incentive programs [19]. It is increasingly suggested that for incentives to both stimulate and sustain health behavior change they should be grounded in theory [19,27,28]. In the single “positive” study, behavioral maintenance (ie, 16-week follow-up) was driven entirely by the lower active subgroup (ie, university students visiting the gym fewer than once per week at baseline)—possibly because exposure to the new behavior (ie, gym attendance) led to increased confidence to perform that behavior [25]. This presumption aligns well with self-determination theory, a global theory of motivation focused on the extent to which behaviors are done volitionally, which suggests that incentive programs designed to increase a person’s confidence are more likely to foster self-determined (or intrinsic) motivation [29,30]—a key driver of sustained physical activity [30].

Realizing the potential of incentives to promote sustained physical activity, therefore, will be contingent on research that improves the understanding of theoretical (eg, self-determined motivation) and contextual (eg, target group characteristics) factors that may influence incentive program effectiveness. The purpose of this protocol is to outline the design of an RCT that will examine the longer term effects of an existing physical activity promotion program that is enhanced by guaranteed incentives for lower active employees only in a real-world, ecological setting. We hypothesize that targeting lower active employees with incentives for tailored daily step goals (in addition to the generic, one-size-fits-all approach to goal setting that is typically used) may be more likely to create mastery experiences, increase confidence, and promote physical activity maintenance.

## Methods

### Study Design

A 12-week, parallel-arm RCT with a 12-week postintervention follow-up will be employed to examine the impact of an enhanced (Can $1 [US $0.74] per day) incentive program on objectively measured physical activity among lower active employees (<10,000 steps per day) within a large Canadian hospital network. See the study flow chart in Figure 1, including an overview of the enrollment process and assessments.

**Figure 1 figure1:**
[figure not shown]
Study flowchart.

### Study Population and Recruitment

This study will specifically target lower active employees (<10,000 steps per day). Hospital employees (including health care professionals and administrative and business support personnel) enrolled in the Change4Life program will be invited to participate via website notifications and hospital newsletters. Only data from participants who accumulate less than 10,000 steps per day during the “2-Week Run-In” period will be included in the analysis. Further eligibility criteria will include: 18 years of age or older, English speaking, ready Internet access, and without medical conditions exacerbated by physical activity as assessed by the Physical Activity Readiness Questionnaire Plus. Eligible participants will be asked to provide their expressed consent using the online consent form.

### Change4Life

Change4Life, a Web- and incentive-based health education and behavior change program, was launched in May 2015 at the hospital network. The hospital network is offering Change4Life to 6500 full-time employees across 8 worksites. Specifically, the Web-based wellness program offers educational information relating to chronic disease prevention via learning modules (ie, series of short articles and quizzes). All employees who sign up for Change4Life are rewarded with points for completing these modules as well as for setting health-related goals, self-reporting health behaviors/outcomes, identifying barriers, and creating action plans—self-regulatory behaviors that have been theorized and empirically proven to promote sustained health behavior change (see the Change4Life Steps Study calendar in Figure 2) [29,30]. Using points, employees may “purchase” ballots in the Change4Life reward store and enter into drawings for health-promoting products (eg, groceries, exercise equipment). At the hospital network, Change4Life operates as a minimal chance-based incentive program (low frequency, low magnitude rewards), where participants have less than a 1 in 100 chance of winning reward drawings that generally range in value from Can $5 to $20 (US $3.70-$14.80).

**Figure 2 figure2:**
[figure not shown]
Change4Life Steps Study calendar (ie, tracking page).

### Standard Care Group

Standard care group participants will have access to Change4Life and will receive the standard minimal chance-based incentives (ie, less than 1 in 100 chance of earning Can $5 to $20 [US $3.70-$14.80] vouchers) for completing learning modules and health tasks. In addition, standard care participants will be asked to wear the accelerometer, which tracks steps and 10-minute bouts of MVPA per day, synchronize the device to the Change4Life program daily, and reach tailored daily step count goals for 10 weeks (weeks 3 to 12). Standard care participants will be instructed to increase their daily step counts by 1000 steps above their baseline average every 2 weeks until they reach the target goal of 3000 extra steps at week 7 (see Table 1). Change4Life will automatically calculate the average baseline value in the early hours of day 1, week 3 using data uploaded the previous 2 weeks (the Run-In period)—days with step counts less than 100 or greater than 50,000 will not be included in calculations [31]. This tailored and graded approach to setting step goals is more realistic than the traditional 10,000 step target (ie, the average Canadian adults accumulates only about 5000 steps per day) [32], may increase chances of intervention success (versus offering a lofty 10,000 step per day goal for everyone), and has worked well in employee populations in the past [33].

**Table 1 table1:** Daily step count goals across the Change4Life program.

Study week	Step count goal
Weeks 1-2	2-Week Run-In (to confirm lower active status and calculate daily step count average)
Weeks 3-4	Increase daily steps by 1000 above baseline average
Weeks 5-6	Increase daily steps by 2000 above baseline average
Weeks 7-8	Increase daily steps by 3000 above baseline average
Weeks 9-12	Maintain steps at 3000 above baseline average

### Intervention Group

The only difference between the standard care and intervention groups will be the addition of the guaranteed incentive (Can $1 [US $0.74] per day). During the intervention period (weeks 3 to 12), intervention group participants will be eligible to earn Can $1 (US $0.74) in vouchers (eg, groceries, coffee, or movies) each time tailored daily step goals are achieved. The total amount available over the intervention period will be Can $70 (US $51.82). Previous research suggests that as little as Can $6.75 (US $5) per week may be sufficient to produce favorable lifestyle health behavior changes [34], thus Can $7 (US $5.18) per week (Can $1 [US $0.74] per day) was chosen as the size of the incentive. During the study follow-up period (weeks 13 to 24), intervention participants will no longer receive the per day reward for reaching daily step goals.

### Outcome Measures

The primary study outcome will be the mean proportion of participant-days that step goals are achieved during week 24 (the postintervention follow-up assessment period, T3). Mean proportion of participant-days that step goals are achieved during week 12 (intervention end point, T2) and volume of steps and 10-minute bouts of MVPA per week at T2 and T3 will be secondary outcomes. Physical activity will be objectively assessed using the StepsCount Piezo Rx accelerometer (StepsCount Inc, Deep River, ON, Canada). The Piezo Rx is a medical-grade device with a single axis piezoelectric sensor. This device has been found to be valid in calculating step counts and MVPA among adult participants [35,36]. Standard care and intervention participants will be encouraged to wear their accelerometer and synchronize it to the Change4Life program during the baseline 2-Week Run-In period (T1), as well as at the intervention end point (T2), and follow-up assessment (T3) with Can $10 (US $7.40) study retention vouchers; these vouchers for assessment completion will help minimize dropout and will not be contingent on step goal achievement.

The adherence outcome variables will be mean number of missing step count entries per week as well as mean number of Change4Life website log-ins in general. Participants’ self-determined motivation to exercise will be examined using the Behavioral Regulation to Exercise Questionnaire-3 (BREQ-3) [37,38]. Participants’ walking self-efficacy will be assessed using a modified version of the Self-Efficacy for Exercise Scale (SEE Scale) [39]. The BREQ-3 and the SEE Scale will be administered online at baseline (T1), intervention end point (T2), and during the follow-up assessment period (T3). The differential impact of the Can $1 (US $0.74) per day incentive on the various physical activity outcomes will be explored. For instance, we may find that while the guaranteed incentives stimulate step goal achievement at T2, they also undermine self-determined motivation and thus the prospect that people will continue to exercise after the incentive is removed.

### Sample Size

Sample size calculations indicate that a final sample of 158 participants (79 per group) ensures 80% power (*P*<.05; 2-tailed) to detect a 0.20 difference in the mean proportion of participant-days step goals are reached between intervention and standard care groups for week 24 [24]. This calculation assumes that the mean proportion of participant-days step goal achieved in the intervention group in week 24 will be 0.40 (vs 0.20 in the standard care group) [24]. On the basis of data published by Patel et al [22] this difference translates into a relative effect size of 0.40. The participant enrollment target will be increased to 174 to account for a potential 10% dropout rate, a rate that has been reported by other similar studies [22,26].

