### Randomization and Blinding

Employees accumulating fewer than 10,000 steps per day during the baseline period (study weeks 1 and 2) will be randomized using a single, constant allocation ratio (1:1) to standard care or intervention groups. Randomization will occur using an online random number generator [40]. Participants will not be blinded to study group allocation. The research analysts will be blinded to group allocation until after the study is completed.

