### Statistical Analyses

For each participant on each day of the study (participant-day level) continuous step count data will be obtained and screened for outliers (less than 100 steps per day, more than 50,000 steps per day) [31]. If participants did not synchronize their accelerometer for at least 3 separate workdays at T2 and T3, the last observation will be carried forward using T1 or T2 means [33]. This procedure conservatively assumes no change in variables and allows analysis by intention-to-treat. The step count data will then be dichotomized at the participant-day level to create a binary variable where participants achieved (value = 1) or did not achieve (value = 0) their step goal. Using this binary variable, the mean proportion of participant-days where step goals were achieved at week 24 will be compared.

SPSS version 21.0 (IBM Corp) will be used to fit a generalized linear model with participant random effects, a random intercept, time-fixed effects (T1-T3), and treatment-fixed effects (by study group). A binomial distribution with logit link for models using the binary outcome will be used to estimate the adjusted difference in the proportion of participant-days step goal achieved, and the bootstrap procedure and resampling of participants will be used to obtain 95% confidence intervals and *P* values. Comparisons across study groups will be adjusted for mean steps per day (baseline), age, gender, and income since these have moderated incentive-effects in the past [41]. The same procedures will be used to analyze T2 (ie, intervention end) binary data.

For continuous step count (ie, mean steps per day) and bout minutes (ie, total minutes of MVPA in 10-minute bouts per week) data at T2 and T3, a generalized linear model will be used, as above, except the difference in steps per day and MVPA bout minutes between groups will be obtained using least-squares means. Also, a repeated measures analysis of variance using linear mixed models with first order autoregressive covariance structures will be used to compare changes in self-determined motivation and self-efficacy between groups. Adherence will be analyzed using *t* tests comparing the mean number of missing step count entries per week and mean number of website log-ins per month between groups. This protocol is registered with ClinicalTrials.gov [NCT02638675].

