### Limitations

This study protocol is not without limitations. First, given that only employees already enrolled in Change4Life (less than 10% of the eligible employee population) will be assessed for eligibility and invited to participate in the study, the results may not be generalizable. By recruiting only lower active Change4Life enrollees, we will learn more about how a higher risk employee population responds to incentives. Since the hallmark of Web-based health interventions is low engagement [49], there is potential for significant study dropout as well (ceasing daily device synchronization and not participating in assessments), especially among standard care participants. Both intervention and standard care participants will be encouraged to participate in all scheduled assessments (baseline, intervention end point, follow-up) with Can $10 (US $7.40) vouchers. Given the low participant burden and potential for lower active individuals to experience improved health, however, this voluntary incentive-based wellness program may be met with relatively high levels of engagement. Finally, participants will not be blinded to study group allocation, which could contaminate the results. Knowledge of group allocation will be assessed using a study exit survey to monitor this potential confounder.

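### The enrollment target of 174 falls slightly short of 158 after 10% dropout, and the allowance is not tied to the carry-forward rule that keeps dropouts in the analysis

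*Protocol article*

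**What the plan says.** Sample Size in the protocol article states that "a final sample of 158 participants (79 per group) ensures 80% power" at a two-sided 5% level. One planning value reads: "the mean proportion of participant-days step goal achieved in the intervention group in week 24 will be 0.40". The comparison value for standard care is 0.20. It then adds the attrition allowance: "The participant enrollment target will be increased to 174 to account for a potential 10% dropout rate". The 10% is attributed to similar studies.

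Statistical Analyses says what happens to participants with too few synchronized workdays at T2 or T3: their T1 or T2 mean is carried forward. The article says that this "allows analysis by intention-to-treat". Dichotomizing into goal met or not met comes after that step.

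Limitations describes dropout as stopping synchronization and not taking part in assessments, and remarks that "there is potential for significant study dropout as well (ceasing daily device synchronization and not participating in assessments), especially among standard care participants". The same paragraph describes retention vouchers and allows that engagement may turn out relatively high.

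**The concern.** There are two separate issues.

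The first is arithmetic. An allowance meant to leave 158 after losing a fraction d must divide by (1 − d). Multiplying by (1 + d) always falls short. The stated target therefore misses the article's own required number.

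The second is a mismatch between sections. Adding people on top of a required final number makes sense mainly if dropouts contribute nothing to the analysis. Under the carry-forward rule they do contribute. The people whom Limitations describes as dropouts are the ones that rule fills in. The number analysed is then not reduced, and attrition acts on the size of the group difference instead. A participant filled with the T1 mean is assigned the baseline average. The goals in Table 1 are set 1000 to 3000 steps above that average, so the filled value cannot meet the goal. At stake is whether the quoted 80% power describes the analysis that will be run.

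**Working it through.** **Inputs.** From Sample Size: 0.40 and 0.20, two-sided 5%, 80% power, 158 final, 174 enrolled, 10% dropout. From Randomization and Blinding: participants are "randomized using a single, constant allocation ratio (1:1) to standard care or intervention groups". The article states no variance. The binary variance p(1 − p) is used below because it reproduces the stated 79 per group.

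**Reproducing 158.** With unpooled variance,

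n = [0.40 × 0.60 + 0.20 × 0.80] × (1.960 + 0.842)² / 0.20² = 78.49, so 79 per group and 158 in total. This matches the article exactly. The pooled-variance formula gives 82 per group and does not match.

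**Reproducing 174.** 158 × 1.10 = 173.8, rounded to 174.

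**Checking 174 against its purpose.**
- 174 × 0.90 = 156.6 (78.3 per group), which is 1.4 below 158.
- 1 − 158/174 = 9.2%, the largest dropout that 174 covers.
- 158 / 0.90 = 175.6, so 176 (88 per group). 176 × 0.90 = 158.4.

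**Power if dropouts leave the analysis.** Power = Φ(0.20 / √(0.40/n) − 1.96).
- n = 79: 80.3%.
- n = 78.3: 79.9%.

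The loss is about 0.4 points. The pooled formula gives nearly the same loss (78.9% to 78.5%).

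**Power if dropouts are kept (87 per group).**

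| Assumption about the 10% carried forward | Proportions | Power |
|---|---|---|
| Difference undiluted | 0.40 vs 0.20 | 83.9% |
| All filled from T1, equally in both arms, scoring zero | 0.36 vs 0.18 | 78.0% |

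For the second row: 0.40 × 0.90 = 0.36 and 0.20 × 0.90 = 0.18. The variance sum is 0.36 × 0.64 + 0.18 × 0.82 = 0.378. Power is Φ(0.18 / √(0.378/87) − 1.96) = Φ(0.77) = 78.0%. Restoring 80% in that scenario would take 0.378 × 7.849 / 0.18² = 91.6, so 92 per group or 184 in total. Moving from 174 to 176 would not restore it.

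**T2 carried to T3.** The week-12 value is recorded while the incentive is still being paid. Carrying it to week 24 could dilute, preserve or inflate the difference. The article gives no figures that would settle which.

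**The case against.** The arithmetic slip is two participants, or 1.1% of the target. The unrounded requirement is 2 × 78.49 = 156.98, so 156.6 is about 0.4 of a person short of it. The 10% is itself only described as potential. All of this stands: the slip is a wrong figure, not a sample-size failure.

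Sample Size does not say that dropouts are excluded. That is inferred from the way the allowance is built. Extra enrollment can also serve to offset dilution under intention-to-treat, so inflating the target and keeping dropouts are not strictly contradictory. This stands too. What remains is that the article does not say which purpose the allowance serves, and the calculation as shown covers only lost numbers.

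The 78% figure is a scenario. It needs all the carried-forward participants to be filled from T1, in equal shares across arms, and it assumes that 0.40 and 0.20 do not already count missing days as goal not met. With unequal T1 filling the difference is 0.40(1 − d₁) − 0.20(1 − d₂), where d₁ is the share filled in the intervention group and d₂ the share in standard care. This equals 0.20 again when d₂ = 2d₁. Limitations raises more dropout in standard care, so dilution is not assured. The between-person variance of a proportion taken over several days is also at most p(1 − p), so these powers are at the low end for a given difference.

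A reader might infer that Limitations contradicts the 10%. It does not: it names a possibility, gives no rate, and also allows for good engagement.

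**Conclusion.** The point holds at minor severity. It is certain that 174 is 158 × 1.10, leaves 156.6 after 10% loss and covers 9.2%; the cost is about 0.4 points of power. It is also established that the allowance is not connected to the carry-forward rule. Depending on how the 10% are filled, power with 174 analysed is about 84% (undiluted) or about 78% (all from T1, equally in both arms, week-24 goal above baseline). Both figures rest on the binary variance inferred from the stated 79 per group.

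A reader might infer that the two issues compound into a materially underpowered trial, with power falling steeply as dropout rises. The document does not support that. If dropouts leave, the carry-forward effect does not arise; if they stay, the shortfall below 158 does not arise. A steep fall would require every dropout to be filled from T1, at rates above 10% that the article does not give. The direction under T2 carry-forward is unknown.

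**What to change.** 1. State the target as 176 randomized after the run-in (88 per group), or keep 174 and say that it covers about 9% dropout.
2. Say whether participants with carried-forward values count toward the 158.
3. Restate power at 10% dropout under the missing-data method actually used, giving the assumed split between T1 and T2 filling and between arms. Any higher rates should be labelled as assumptions.

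The cost is a few restated figures and at most two more participants. Step 1 alone corrects only the arithmetic; steps 2 and 3 deal with the mismatch.
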